## Methods and design

### Objectives

The primary objective is to conduct a multicentre trial to investigate clinical effectiveness of KJD compared with KR in patients aged 65 years or less, with symptomatic knee OA severe enough to warrant KR, based on patient reported pain 12 months after surgery.

Secondary objectives are to investigate: (1) patient-reported outcomes, (2) clinical outcomes of knee function, (3) complications and need for further intervention, (4) cost-effectiveness, (5) participant experiences, intervention fidelity and barriers to wider implementation.

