##### Secondary outcome measures

*Patient report outcome measures (PROMs) and QoL within 24 months post-surgery*
KOOS (overall and at component level).Pain Visual Analogue Scale (VAS).^26 27^Oxford Knee Score (OKS). 28–30
*Objective assessment of knee function*
Active range of movement.Timed-up-and-go test.^31 32^
*Incidence of complications, including infection*
Intra-operative complications.Post-operative complications.^33^
*Further interventions within 24 months postsurgery*
Further surgical interventions including conversion to KR or revision surgery.
*KJD’s potential as cartilage regenerative therapy*
Joint space width (assessed using standardised fixed flexion PA at 20^o^ X-rays^34^).
*Estimate of short-term and long-term cost-effectiveness*
EuroQol 5 Dimensions (EQ-5D)-3L questionnaire at 24 months.Health Resource Utilisation and Private Costs questionnaire at 24 months.Incremental costs per QALY gained at 20 years.Implementation processes and intervention fidelityQuantitative (surgical CRF and central review of post-operative X-rays).Qualitative evaluation with surgical and clinical staff.Qualitative evaluation of participant experiences.

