#### Analysis methods

Full statistical analysis plan predefining all analyses and patient populations will be in place prior to any comparative analyses according to guidelines.^41^ KARDS will be reported according to the Consolidated Standards of Reporting Trials extension for Non-Inferiority and Equivalence Randomised Trials.^42^ The intention-to-treat (ITT) population will include all randomised participants, and the per-protocol (PP) population will include all participants who received their randomised intervention as intended. Although there is no ‘gold standard’ for non-inferiority trials, outcomes will be analysed primarily for the PP population.^43^ A sensitivity analysis will be conducted for the ITT population.

The primary analysis will report adjusted estimates of treatment effect from multivariable regression of KOOS pain score at 12 months. Statistical significance of KJD non-inferiority relative to KR will be based on a 2-sided likelihood-based test with type 1 error of 2.5% in both tails, adjusted by baseline score and OA severity as fixed effects, and delivery unit as a random effect.^44^ If the 95% confidence interval (CI) for absolute difference in means between KJD and KR lies entirely below or includes the non-inferiority boundary, then there would be insufficient evidence to reject the null hypothesis that KJD inferior to KR. Conversely, if the 95% CI lies entirely above the non-inferiority boundary, there would be evidence to reject the null hypothesis and conclude KJD non-inferior to KR. If non-inferiority demonstrated and KJD appears superior to KR, based on estimated effect and associated CI, statistical significance for superiority will be calculated based on an ITT analysis. Secondary analysis of the primary outcome measure will use multilevel modelling to account for longitudinal data collected over 24 months. Sensitivity analyses will be considered to investigate any impact of surgeon experience on treatment effect estimates.^45^

Reasons for missing data will be examined and primary method to account for missing data will be chosen based on the most reasonable missing data mechanism assumption, with sensitivity analyses to assess robustness of results to different missing data mechanism assumptions.

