Other PROM responses will be transformed into dimension scores, according to scoring manuals, and presented graphically and longitudinally. Standardised area under the curve (AUC) statistics will be compared across treatment groups as an analysis conditional on patient time in the trial. Functional assessments will be reported descriptively, along with joint space width for the KJD group.

Complications will be reported as unique events and unique patients experiencing events. Joint survival will be measured from randomisation to time of further intervention and analysed using the Kaplan-Meier method.

Process evaluation interview data will be analysed using thematic content analysis to identify patterns or themes,^46^ using coding of audio-transcript recordings, adopting the framework method described by Ritchie and Spencer and Pope and Mays.^47 48^ Normalisation Process Theory will be used as a theoretical framework to explore and explain extent of intervention implementation,^49–51^ using the software package NVivo V.12 to manage data and facilitate this process. Interview data and full record of issues raised will be discussed in detail with the Trial Management Group and summarised for oversight committees. Good practice will be shared with other recruiting sites.

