The most frequently reported KJD complication is pin site infection. Rates approaching 70% have been reported, with 20% of affected patients requiring intravenous therapy.^64^ In the series of 62 patients described above, two patients required surgical intervention for pin-site infection during distraction, with a further case of osteomyelitis requiring surgery following fixator removal.^11 17 19^ These infection rates are at odds with those reported in patients treated by definitive external fixation for other reasons. Pin-site infection rates of 40% are found fairly consistently, even where fixators are in place for much longer, the reasons for this are unclear.^66^ While transient pin-site infection seldom has long-term implications, it is unpleasant for patients and may impair rehabilitation. Deep infections may be more worrisome, especially considering expected osteoarthritis progression following distraction potentially requiring eventual arthroplasty. Wherever possible, external fixator pins will be sited outside the implantation zone of a KR. Total KR following significant osteomyelitis is significantly more complex and has further infection risk even when infection considered eradicated.^67^ Current KJD literature does not provide sufficient evidence to estimate serious infection rates following conversion to KR. In one ankle distraction study with over 5-year follow-up, there was no infection seen in five patients who had conversion to arthroplasty.^68^ Loss of knee range of movement immediately following distraction therapy has been observed to return after 1 year, with a small number of patients undergoing joint manipulation under anaesthetic to achieve this.^13 19^

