Trial strengths include its pragmatic nature, standardised surgical and assessment techniques, robust reporting and safety mechanisms and appropriate sample size. The window of 6 weeks between baseline measures and planned surgery date aligns with clinical pathways and ensures recruitment feasibility. KARDS has a pragmatic hybrid expertise-based design, where surgeons are categorised into ‘delivery units’ based on their experience, a successful approach in similar knee OA surgical trials.^69^ Furthermore, clinicians are free to choose KR implant type and KJD external fixator. This choice brings a limitation in not being able to determine potential individual mechanisms of action limiting individual indications and/or contraindications. Those implants and fixators approved in the trial protocol are based on consensus among experts and published literature. Subgroup analysis will not be adequately powered to determine if a particular fixator type is superior. A further limitation is the lack of blinding, but this is unavoidable. It would be impractical to blind medical staff prior to surgery at many sites as they need to plan for the specific surgery. PPI feedback was that being blinded until just before or after surgery would be unacceptable if the medical team knew the allocation. The primary outcome measure is patient reported and, therefore, it is not possible to have a blinded primary outcome assessment.

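### The only function measures that are not self-reported, range of movement and timed-up-and-go, are to be described only, so the knee-function objective gets no planned adjusted KJD-KR difference with a confidence interval

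*Protocol article*

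**What the plan says.** The Objectives section of the protocol article lists, separately from patient-reported outcomes, the item "2) clinical outcomes of knee function". Under Secondary outcome measures, the group headed "Objective assessment of knee function" has two entries: "Active range of movement.Timed-up-and-go test".

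For these the Analysis methods section states: "Functional assessments will be reported descriptively, along with joint space width for the KJD group". The same paragraph treats the other patient-reported outcomes differently: "Standardised area under the curve (AUC) statistics will be compared across treatment groups".

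For KOOS pain at 12 months, the section specifies a regression "adjusted by baseline score and OA severity as fixed effects, and delivery unit as a random effect". Under Randomisation and blinding, OA severity and delivery unit are the two minimisation factors, and participants, medical staff and trial staff all know the allocation. The Data collection section places clinical data collection in both arms at baseline and at months 3, 12 and 24 after surgery. The visit-by-visit schedule is in a supplement that is not shown.

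**The concern.** Descriptive reporting of functional assessments is a stated choice, not a detail left open. The two function tests are the only evidence on function that does not pass through a questionnaire. The trial is open label, and the Discussion concedes the consequence for the main endpoint: "The primary outcome measure is patient reported and, therefore, it is not possible to have a blinded primary outcome assessment". KOOS and the Oxford Knee Score share that limitation. The two tests are less exposed to what participants believe about their allocation, and they are the outcomes with no planned between-arm estimate.

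Movement is also a live question for distraction. The Discussion reports early loss of range of movement after KJD, and the Intervention section includes an attempt at manipulation when the fixator is removed. If KJD proves non-inferior on pain, readers will ask how much range of movement or walking speed differs from KR, and with what uncertainty. As written, the plan commits to no interval that answers this.

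**Working it through.** **1. What is planned for each outcome**

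| Outcome | Type | Planned comparison |
|---|---|---|
| KOOS pain, 12 months | self-report | adjusted difference with 95% CI |
| Other patient-reported outcomes | self-report | standardised AUC compared between arms; no adjustment stated |
| Range of movement, timed-up-and-go | measured | descriptive |
| Joint space width | structural | descriptive, KJD only |

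The two measured function outcomes have no stated between-arm estimate. Joint space width is structural and described in one arm, so it does not fill the gap.

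**2. The plan's own sample size.** Inputs from the Sample size section: margin 8, SD 21, one-sided 2.5%, power 90%, dropout 15%, 172 per arm.

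- n per arm = 2 × (1.96 + 1.2816)² × 21² / 8² = 144.8, so 145.
- Dropout: 145 / 0.85 = 170.6, so 171 per arm and 342 in total, against 344 stated. This reproduces to within two participants.
- In reverse, 172 × 0.85 = 146.2 evaluable per arm, which gives power of 90.3%.

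**3. Precision available for the function tests.** The article gives no SD or baseline correlation for them, so results are in SD units. With r the assumed correlation between baseline and follow-up:

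95% CI half-width = 1.96 × √[(2/n) × (1 − r²)]

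| Evaluable per arm | r = 0 | r = 0.5 | r = 0.7 |
|---|---|---|---|
| 146 (15% loss) | 0.229 | 0.199 | 0.164 |
| 120 (30% loss, assumed) | 0.253 | 0.219 | 0.180 |

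For example, 1.96 × √(2/146) = 0.229, and 0.229 × √(1 − 0.25) = 0.199. At r = 0.5 the variance falls by 25%, which is worth as much as 146 / 0.75 ≈ 195 participants per arm without adjustment.

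**4. Reading.** Over this range the half-width is 0.16 to 0.25 SD. Trial size gives no reason to stop at description, and adjustment gives a modest gain in precision.

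**The case against.** The case for leaving the plan alone has real weight.

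- *No contradiction.* The secondary objectives are framed as matters to investigate. That promises no hypothesis test, and description is compatible with it. This stands. A reader might infer that the knee-function objective is left unanswered, but the documents do not support that: summaries by arm would give a crude contrast, and minimised randomisation makes it usable. One limit is that outcomes are to be analysed primarily in the per-protocol population, where the arms are not fully protected by randomisation.
- *The recovery statement.* A reader might take "Loss of knee range of movement immediately following distraction therapy has been observed to return after 1 year" as a claim about KJD against KR that the trial should test. It describes recovery within KJD patients and makes no comparison with KR. The between-arm question is a natural one, but that sentence does not state it.
- *Function is compared elsewhere.* KOOS components and the Oxford Knee Score are among the patient-reported outcomes to be compared between arms. So it would be wrong to say that the trial can say nothing about function. What is missing is the comparison that is not self-reported.
- *Adjustment.* The AUC comparison is not said to be adjusted either, so the contrast with those outcomes is between comparison and description, not between adjusted and unadjusted analysis.
- *Bias.* A reader might infer that the two tests are free of bias from knowledge of allocation. Both depend on effort, and neither participants nor staff are blinded. They are less exposed than questionnaires, no more than that.
- *The unseen analysis plan.* It is to predefine all analyses and may add these estimates. That is possible, but the published text commits to description.

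**Conclusion.** The point holds as a modest, cheap improvement. The plan describes the only function measures that are not self-reported while comparing the questionnaires between arms. The knee-function objective is therefore answered less precisely than the data allow, with no planned adjusted difference and interval.

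The size of what is lost is limited: a half-width of about 0.23 SD unadjusted and 0.20 SD adjusted at r = 0.5, none of which the plan undertakes to report. These figures assume that the 15% dropout set for KOOS pain also applies to clinic-measured tests (giving 146 per arm), that r is about 0.5, and that both tests are done at baseline and at the month 3, 12 and 24 visits. The primary conclusion and the sample size are unaffected.

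**What to change.** For active range of movement and timed-up-and-go, report the adjusted KJD-KR difference with its 95% CI at each scheduled post-operative clinical visit (months 3, 12 and 24 if the tests are done then). Use the structure of the primary model: baseline value and OA severity as fixed effects, delivery unit as a random effect. Label the results supportive, with no confirmatory claim, and keep joint space width descriptive in the KJD arm.

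The cost is one change of wording in the analysis plan and up to six regressions (two measures at three visits) on data already due to be collected. The downside is a few more secondary intervals to interpret. If the sponsor prefers description only, the knee-function objective should be reworded as descriptive so that objective and analysis agree.

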### Monitoring

An independent Trial Steering Committee (TSC), comprising a statistician, two orthopaedic consultant surgeons and one patient representative, will have overall responsibility for trial oversight, monitoring trial progress, protocol adherence and participant safety. An independent Data Monitoring and Ethics Committee (DMEC) comprising a statistician and two orthopaedic consultant surgeons will review interim safety data by randomised group, reviewing the underlying statistical design assumptions to ensure the trial remains adequately powered. TSC and DMEC meetings will be conducted annually as a minimum according to agreed TSC and DMEC Charters.^61^

No formal guidelines for stopping the trial early are in place since no formal planned interim analysis of the primary outcome is planned.

Information on complications will be collected from randomisation to end of trial defined as the last visit date of the last patient. Serious complications will be subjected to expedited reporting where sites will inform CTRU within 24 hours of becoming aware of it. Suspected or confirmed pregnancies and all deaths from randomisation until the end of trial will be reported to CTRU.

## Ethics and dissemination

KARDS is funded by NIHR HTA (reference: 17/122/06) and sponsored by the University of Leeds, approved by the Research Ethics Committee (REC) (reference: 19/YH/0368) and Health Research Authority (HRA). All amendments will be submitted for approval and communicated to sites in accordance with HRA guidelines.

Trial results will be disseminated at relevant clinical conferences and societies, published in peer-reviewed journals and disseminated through relevant patient groups. Authorship will be according to International Committee of Medical Journal Editors (ICMJE) guidelines.

## Discussion

KARDS is a pragmatic, multicentre prospective randomised controlled trial conducted in an NHS setting, the aim is to determine if KJD is non-inferior to KR in terms of pain and cost-effective in the NHS, then it could be routinely offered to patients aged 65 years or less. In addition, it will report on radiological outcomes and patient acceptability. It will be a definitive IDEAL stage 3 (Assessment) trial^21^ with potential to lead to a paradigm shift if it demonstrates non-inferiority of KJD compared with KR.

Joint distraction outcomes at various anatomical locations have been reported in several case series. Though small numbers of patients have been involved, results are encouraging in at least providing temporary symptom relief. At the ankle, improvements in reported symptoms were seen in 73%–91% of patients at mean follow-up time of 1–12 years.^62^ Joint distraction has been demonstrated to give good clinical outcomes in first carpometacarpal joint osteoarthritis, albeit in a very limited number of patients. Patients were followed for 1 year with improved functional scores compared with baseline.^63^ The KJD literature is difficult to assess due to heterogeneity of devices and methods used. A recent review included one cohort study and two small trials all of which came from the same research group, including a total of 62 patients.^64^ These studies all utilised a spring-loaded static distractor. Western Ontario and McMaster Universities Osteoarthritis Index score improvements were significantly greater 1 year post KJD than conservatively managed osteoarthritis,^17^ and not inferior to total KR^19^ or high tibial osteotomy (HTO).^11^

Two studies^11 19^ reported KOOS, Intermittent and Constant Osteoarthritis Pain score, EQ-5D and Short Form (SF)−36 with significant improvements at 1 year seen in all scores except for the SF-36 mental component score, with no significant difference in these improvements compared with KR or HTO. Pain score assessed on pain VAS was reported in both studies and showed improvements at 1 year with no significant difference between KJD and HTO or KR. Radiographic assessment of joint structure has been undertaken in various studies, with imaging at the time of distraction or follow-up. The group above used MRI to assess structural recovery. Mean cartilage thickness was shown to increase on both the tibial and femoral sides and percentage of joint surface appearing as denuded subchondral bone decreased.^64^ Radiographic minimum joint space width was shown to increase by 0.8 mm at 12 months compared with baseline.^11 17 19^ Similar to another study where the mean joint space width, measured using standardised digital techniques, increased from 2.7 mm to 3.6 mm 12 months post-fixator removal.^65^

The most frequently reported KJD complication is pin site infection. Rates approaching 70% have been reported, with 20% of affected patients requiring intravenous therapy.^64^ In the series of 62 patients described above, two patients required surgical intervention for pin-site infection during distraction, with a further case of osteomyelitis requiring surgery following fixator removal.^11 17 19^ These infection rates are at odds with those reported in patients treated by definitive external fixation for other reasons. Pin-site infection rates of 40% are found fairly consistently, even where fixators are in place for much longer, the reasons for this are unclear.^66^ While transient pin-site infection seldom has long-term implications, it is unpleasant for patients and may impair rehabilitation. Deep infections may be more worrisome, especially considering expected osteoarthritis progression following distraction potentially requiring eventual arthroplasty. Wherever possible, external fixator pins will be sited outside the implantation zone of a KR. Total KR following significant osteomyelitis is significantly more complex and has further infection risk even when infection considered eradicated.^67^ Current KJD literature does not provide sufficient evidence to estimate serious infection rates following conversion to KR. In one ankle distraction study with over 5-year follow-up, there was no infection seen in five patients who had conversion to arthroplasty.^68^ Loss of knee range of movement immediately following distraction therapy has been observed to return after 1 year, with a small number of patients undergoing joint manipulation under anaesthetic to achieve this.^13 19^

Trial strengths include its pragmatic nature, standardised surgical and assessment techniques, robust reporting and safety mechanisms and appropriate sample size. The window of 6 weeks between baseline measures and planned surgery date aligns with clinical pathways and ensures recruitment feasibility. KARDS has a pragmatic hybrid expertise-based design, where surgeons are categorised into ‘delivery units’ based on their experience, a successful approach in similar knee OA surgical trials.^69^ Furthermore, clinicians are free to choose KR implant type and KJD external fixator. This choice brings a limitation in not being able to determine potential individual mechanisms of action limiting individual indications and/or contraindications. Those implants and fixators approved in the trial protocol are based on consensus among experts and published literature. Subgroup analysis will not be adequately powered to determine if a particular fixator type is superior. A further limitation is the lack of blinding, but this is unavoidable. It would be impractical to blind medical staff prior to surgery at many sites as they need to plan for the specific surgery. PPI feedback was that being blinded until just before or after surgery would be unacceptable if the medical team knew the allocation. The primary outcome measure is patient reported and, therefore, it is not possible to have a blinded primary outcome assessment.
